**Methods:**

This trial is a monocentric, national, prospective randomized controlled trial aiming to recruit 66 adolescent participants (14–17 years) meeting criteria for insomnia disorder in Germany. Participants will be randomized (1:1) to either 12 weeks of digital CBT-I (*somnio junior)* or sleep hygiene advice. Outcomes will be collected at baseline, 6- and 12-weeks post-randomization. The primary endpoint is self-reported insomnia severity using the Insomnia Severity Index at 12 weeks. Secondary endpoints include symptoms of depression, anxiety, daytime sleepiness and health-related quality of life. Analyzes will be intention-to-treat.

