For adults, there is substantial evidence supporting the effectiveness of digital CBT-I (dCBT-I) (31–33). The use of dCBT-I therefore offers a cost-efficient (34), low-threshold and accessible solution to the treatment gap (35–38). For adolescents, a recent meta-analysis on eight RCTs of CBT-I in adolescents found large treatment effects for insomnia severity [standardized mean difference (SMD) = −1.06], when compared to control (23). Yet, digitally delivered CBT-I interventions for adolescents are barely investigated and, to date, considered preliminary with only four RCTs reporting beneficial effect on sleep and insomnia, when compared to control (39, 40). As discussed by Werner-Seidler and colleagues (41), adolescents may even perceive digital therapy options as more appealing, as they are generally more familiar and comfortable with using digital technologies. Moreover, barriers that often discourage adolescents from seeking help, such as stigma, may be less prominent in digitally delivered interventions. In summary, there is a significant gap in the need and availability of guideline recommended treatment for insomnia in adolescents. Digital solutions may have large potential but are yet lacking substantial evidence. To address this need, a digital application, namely *somnio junior* (mementor DE GmbH), was specifically developed to be investigated, and if proven to be effective, to be integrated into the German health care system.

The primary aim of this randomized controlled trial is to elucidate whether dCBT-I (intervention group, IG) is effective in adolescents diagnosed with insomnia, when compared to sleep hygiene advice (control group, CG).

It is hypothesized that the self-reported insomnia severity (primary endpoint) will decrease in participants of the IG compared to the CG at 12-weeks post-randomization. As secondary endpoints, a decline in symptoms of insomnia at 6-weeks post-randomization and, at 12-weeks post-randomization, a decline of depression, anxiety, daytime sleepiness and an increase in health-related quality of life is expected in the IG, when compared to CG. All variables are measured using self-report questionnaires.

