### Statistical analysis

2.8

The primary statistical analysis will follow the intention-to-treat (ITT) principle. Efforts will be made to collect complete follow-up data for all participants to facilitate a comprehensive ITT analysis. However, missing data may occur due to withdrawals, loss to follow-up, or incomplete responses to some questionnaire items. Trial results will be presented as comparative summary statistics with 95% confidence intervals (CIs), and all tests will use a two-sided significance level of 5%. The study results will be reported in accordance with the Consolidated Standards of Reporting Trials (CONSORT) guidelines (54). A mixed effect linear model based on an unstructured covariance matrix will be fitted to the primary outcome data (ISI at 12 weeks), utilising 6- and 12-week timepoints. Participant will be included as random effects. Fixed effects will include randomized group, baseline ISI score, group, time and a time by randomized group interaction term to allow estimation of treatment effect at each timepoint. Missing data will be reported, including any available reasons for the missingness, and the patterns of missing data will be examined. The mixed-effects model inherently accounts for data assumed to be missing at random. Standard residual diagnostics will be conducted to evaluate the model's suitability. If the assumptions are found to be violated, alternative non-parametric methods will be considered for the primary analysis. Continuous secondary outcomes with only two time point measures (baseline and 12-weeks) will be analyzed with ANCOVA models, adjusting for baseline variable. The estimated difference between the groups after 12 weeks will be derived using a linear contrast statement from the ANCOVA model. Missing data, assuming confirmation of the “Missing at Random” (MAR) condition, will be estimated using multiple imputation. Subgroup analyses will be conducted based on gender (female, male). Secondary count outcomes (e.g., number of responders, number of side effects, number of measures to improve sleep) will be analyzed using Chi-Square tests. For the primary outcome, insomnia severity, a responder analysis will be conducted based on the Minimal Clinically Important Difference (MCID) for the Insomnia Severity Index (ISI), defined as a change in ISI ≥ 8. This analysis will examine differences between groups. Similarly, responder analyses will be conducted for depression [change in PHQ-9 ≥ 5 (47);] and anxiety measures [change in GAD-7 ≥ 3 (55);]. All outcomes were prespecified and are known to be correlated; therefore, consistent with methodological recommendations (56–58), no formal multiplicity adjustment will be applied.

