
The primary outcome measure is insomnia severity 12 weeks post-randomization. Assuming that this outcome follows a normally distributed population and that linear mixed models rely on pairwise comparisons, the hypothesis will be tested using a two-sided t-test for independent samples within a parallel-group design. To detect a statistically significant group difference with a Standardized Mean Difference (SMD) of 1.07 [the lower confidence interval of the within-group effect size reported in a prior study on the efficacy of digital CBT-I in adolescents using the Insomnia Severity Index (59);] with a power of 95% and an alpha level of 0.05, 24 participants per group are required [calculated using G*Power (60);]. Considering an anticipated dropout rate of 27% [based on (59)], a total of 66 adolescents should be randomized for the study.

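### The stated 95% power is not supported by its cited source: a between-group test is powered with a within-group (pre-post) effect size

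*Protocol article*

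**What the plan says.** Section 2.8 (Statistical analysis) of the protocol article frames the sample size around a comparison between arms: "the hypothesis will be tested using a two-sided t-test for independent samples within a parallel-group design". The target is also a between-arm quantity: "To detect a statistically significant group difference with a Standardized Mean Difference (SMD) of 1.07". The bracket that follows gives the origin of 1.07 as "the lower confidence interval of the within-group effect size reported in a prior study on the efficacy of digital CBT-I in adolescents". The result is that "with a power of 95% and an alpha level of 0.05, 24 participants per group are required". An anticipated dropout of 27% then brings the total to 66, with 1:1 allocation.

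Three other places bear on the point:
- Section 2.1 describes the control arm as sleep hygiene advice plus treatment as usual (TAU). Section 2.2 defines TAU as any ongoing medical or psychological care, including psychotherapy and medication.
- Section 2.8 makes the primary analysis a mixed model on the 6- and 12-week ISI scores with baseline ISI as a fixed effect, not an unadjusted t-test.
- The Background contains the only numerical between-group SMD in the article: "a recent meta-analysis on eight RCTs of CBT-I in adolescents found large treatment effects for insomnia severity", with SMD −1.06 against control. The sample size paragraph does not refer to it.

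**The concern.** A within-group effect is the change from before to after treatment in treated participants. It includes the treatment effect and everything else that moves scores over the same weeks: natural improvement, regression to the mean in people enrolled because they have insomnia, and non-specific effects of taking part. Those parts also arise in a control arm and cancel in the between-arm difference that the primary test estimates. A pre-post effect may also be divided by a different SD, for example the SD of change.

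Planning with the lower confidence limit looks cautious, but it guards only against sampling error in the pre-post effect. It does not allow for change in the control arm.

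This is the only power statement in the article and it concerns the single primary endpoint. If the true between-group effect is moderate, a non-significant result could be read as absence of benefit on the strength of a 95% power claim whose source does not support it.

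**Working it through.** **Inputs.** From the article: SMD 1.07, two-sided α = 0.05, power 95%, 1:1 allocation, dropout 27% (section 2.8 and the Abstract); between-group SMD −1.06 (Background). Assumed here, because the article does not give them: the size of any control-arm change, the baseline-to-outcome correlation r, and the SD used to standardise the cited effect.

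**1. Reproducing the plan's figure.** For a two-sample t-test with n per arm, power is the probability that a non-central t variable with 2n − 2 degrees of freedom and non-centrality d·√(n/2) exceeds the two-sided 5% critical value in absolute size.
- d = 1.07, n = 24: non-centrality 1.07 × √12 = 3.71, 46 df, power 95.2%. With n = 23, power is 94.4%. So 24 per arm is correct.
- Dropout: 48 / (1 − 0.27) = 65.75, so 66.
- A paired test with 1.07 as a standardised change would need only 14 participants in total. The stated 24 per arm is therefore the independent-groups calculation, with the within-group value entered as a between-group SMD.

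**2. Power at other between-group SMDs, 24 evaluable per arm.** The adjusted column replaces d by d/√(1 − r²) with r = 0.5, so d/0.866. It ignores the one degree of freedom spent on the covariate.

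| Between-group SMD | Unadjusted t-test | Baseline-adjusted, r = 0.5 |
|---|---|---|
| 1.07 | 95% | 99% |
| 0.9 | 86% | 94% |
| 0.8 | 77% | 88% |
| 0.6 | 53% | 65% |
| 0.5 | 40% | 50% |

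**3. Detectable SMD, 24 evaluable per arm.** Each adjusted value is the unadjusted value × 0.866.

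| Power | Unadjusted | Baseline-adjusted, r = 0.5 |
|---|---|---|
| 80% | 0.83 | 0.72 |
| 90% | 0.96 | 0.83 |
| 95% | 1.06 | 0.92 |

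**4. What a control-arm change would do (illustration).** Assume both changes are on the same SD scale, so that between-group SMD = 1.07 − control-arm change. Unadjusted power at 24 per arm:
- change 0: SMD 1.07, 95%
- change 0.2: SMD 0.87, 84%
- change 0.3: SMD 0.77, 74%
- change 0.4: SMD 0.67, 62%
- change 0.5: SMD 0.57, 49%

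**5. What the standardiser would do (illustration).** Suppose the control arm does not change but 1.07 was standardised by the SD of change. Then the SMD on the between-person scale is 1.07 × √(2(1 − r)), with r the pre-post correlation:
- r = 0.7: SMD 0.83, power 80%
- r = 0.5: SMD 1.07, power 95%
- r = 0.3: SMD 1.27, power 99%

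This second uncertainty can move power either way.

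**6. The article's own between-group figure.** SMD 1.06 at 24 per arm gives 94.9% unadjusted and 98.6% adjusted at r = 0.5.

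**The case against.** The strongest reply is that the number may be about right even though its source is not. The Background's −1.06 against control, from eight adolescent trials, gives almost the same power. The Discussion cites a suggestion that digital CBT-I has effects comparable to group CBT-I, and section 2.3 reports large effects against control for the adult version of the product. This stands to the extent that a materially wrong sample size is not shown. It does not repair the justification. The −1.06 is not the stated basis. It is a point estimate, so planning at that level leaves no margin. It covers adolescent CBT-I in general against unspecified control, not digital delivery against sleep hygiene advice, and the Background itself calls the digital evidence in adolescents preliminary.

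A second reply is that the unadjusted figures understate the planned analysis, which adjusts for baseline ISI and also uses the 6-week scores. Participants with only a 6-week score still contribute to it. This is correct, which is why the adjusted column is shown. At r = 0.5 it recovers part of the loss, but power at SMD 0.6 is still only 65%.

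A reader might go further and infer that the trial is underpowered, or that 95% is false for the primary comparison. The article does not support that. The calculation is right conditionally on a between-group SMD of 1.07, and neither the control-arm change nor the standardiser in the cited study is given.

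**Conclusion.** The point holds as a defect of justification. The 95% power claim rests on a within-group effect used as a between-group SMD, and nothing in the article bridges the two. The arithmetic from SMD 1.07 to 24 per arm and 66 in total is correct. Actual power is unknown. It stays near 95% if the between-group effect is about 1.06 or larger. It falls to between 40% (unadjusted) and 50% (adjusted) if the effect is 0.5. The adjusted figures depend on the assumed r = 0.5, and all figures assume 24 evaluable participants per arm. Type I error, the primary model and the treatment estimate are unaffected, and the planned 95% confidence intervals partly protect against misreading a null result. No conclusion that N = 66 is too small follows from the article.

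**What to change.** Keep N = 66 and rewrite the sample size paragraph of section 2.8:

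- Remove the within-group effect as the justification for 1.07.
- State either the between-group SMD assumed for digital CBT-I against sleep hygiene advice plus TAU, with its source, or the control-arm change assumed and the SD scale used. The value cannot be supplied from the article, so the sponsor must choose and defend it. If −1.06 is adopted, say that it is a general CBT-I estimate.
- Replace the unqualified 95% claim by the power that 24 evaluable per arm gives over SMDs from 0.5 to 1.07. Show the baseline-adjusted figures, with the assumed correlation named, beside the unadjusted ones, and give the detectable SMDs (adjusted 0.72, 0.83 and 0.92; unadjusted 0.83, 0.96 and 1.06 for 80%, 90% and 95% power).

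The cost is one rewritten paragraph and a short table, with no extra participants. The downside is that the stated power becomes less favourable.

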## Discussion

3

Despite the high prevalence of insomnia in adolescents and the wide range of associated problems, there is still no sufficient and adequate treatment for this target group. Although CBT-I as method of first choice is well validated (22, 23), too few children and adolescents receive access to this intervention (29). Tackling this care gap, digital interventions implementing CBT-I are evaluated in different studies (61–63) and meta-analyses reveal promising prospects of these interventions (31, 40, 64). De Bruin and colleagues (34) suggest that dCBT-I is a more cost-efficient therapy option and effects are comparable to CBT-I in a group setting.

If proven efficacious, the dCBT-I *somnio junior* aims to provide an economic and guideline-based treatment for adolescents suffering from insomnia. A strength of the current study is the clearly defined target population. While existing literature often includes samples ranging from general sleep problems to full insomnia symptoms—resulting in challenges for interpretation and comparability—the present study is based on a clinical diagnosis of insomnia made by a physician, according to DSM-V criteria. Therefore, results of this study can be directly applied to insomnia requiring treatment. With a bidirectional relationship between insomnia and mental disorders as depression, anxiety disorder (19) or other social-emotional and behavioral problems (14, 15), treating insomnia might also positively affect associated problems (65) as it was found to be a significant predictor for mental disorders as depression and anxiety (66). One possible mechanism connecting insomnia and mental health issues might be a compromised emotional regulation, which was found in people with sleep deprivation. Problems with regulation of emotion is a common underlying factor of psychiatric disorders (67). Indeed, next to symptoms of mental disorders, sleep deprivation is associated with emotional reactivity (68) and impulse control (17). Further, decreased sleep duration is a risk factor for several physical health concerns, including functional cortical alterations and systemic inflammation, hypertension, coronary artery disease, diabetes or obesity, and increased all-cause mortality (1, 12, 13). Thus, early treatment of insomnia might not only prevent chronification of insomnia symptoms, but might also have a preventative effect, so that subsequent disorders are less likely to occur. This could also be relevant for adolescents waiting for a psychotherapeutic treatment. The clear influence of sleep on physical health further undermines the importance of adequate treatment.

Accounting for these proposed associations, this study will evaluate both effects of the dCBT-I *somnio junior* on insomnia severity and on the related measures (daytime sleepiness, depression, anxiety and health-related quality of life). If the study shows the proposed effects *somnio junior* can be implemented as an economic, theory- and guideline-based intervention for the treatment of insomnia in adolescents.

### Limitations

3.1

Due to the lack of a follow-up assessment, we will not be able to make assumptions on long-term effects of the application *somnio junior*. Since in most studies on dCBT-I, there were no changes from post- to follow-up assessment, we can assume, that this will be the case in the present study as well. However, future studies should evaluate long-term effects. Another limitation is that the intervention (interactive dCBT-I app) is contrasted with a low-intensity control (sleep hygiene flyer), resulting in unequal engagement and participant contact. This may introduce expectancy or attention effects that could contribute to observed differences. However, the comparator reflects minimal-care conditions typical of routine practice and avoids introducing additional active components. Furthermore, this study relies exclusively on validated self-report measures and sleep diaries. While the inclusion of objective monitoring (e.g., actigraphy) would have allowed for additional characterization of sleep–wake patterns and subjective–objective concordance, this was beyond the scope of the present study, which focused on perceived sleep difficulties and related distress—core features of insomnia as defined by the DSM-5. Future research may incorporate objective measures to address complementary questions regarding sleep physiology and circadian patterning. Lastly, we have planned exploratory analyses that are based on sleep diary data collected within the digital intervention only. As completion of the sleep diary is integrated into the application and forms part of the intervention, participants in the control group do not complete corresponding diary entries. Consequently, these data cannot be compared between groups, which substantially limits the interpretability of the exploratory analyses. Despite this constraint, the study is designed to provide meaningful evidence on whether dCBT-I *somnio junior* is effective in reducing insomnia symptoms and related outcomes in adolescents.

### Further directions

3.2

If proven efficacious, the dCBT-I *somnio junior* provides an economic and guideline-based treatment for adolescents struggling with insomnia. In this case, *somnio junior* will be implemented as a digital health application (Digitale Gesundheitsanwendung; DiGA) and practitioners will be able to prescribe this DiGA for adolescents struggling with insomnia. Future studies should evaluate long-term effects and effects on objective sleep parameters. Next to the application for adolescents, a version of the dCBT-I tailored for parents supporting their children struggling with insomnia could further enhance the effectiveness of the intervention.

### Trial status

3.3

In progress, recruiting.
